### Plans to give access to the full protocol, participant-level data and statistical code {31c}

Participant-level data and statistical code generated during the current study will be available from the corresponding author upon reasonable request up to five years after completion of the trial.

## Oversight and monitoring

### Composition of the coordinating center and trial steering committee {5d}da

Screening and recruitment are conducted under the supervision of the PMG, which includes the PI, study coordinator, and designated research staff, including research interns and RDs. The PMG meets weekly to review trial conduct and monitor overall progress. All other study-related procedures are implemented by trained members of the PI’s team, who maintain daily communication to ensure coordinated and efficient trial operations. The Steering Committee, comprising the PI, senior investigators, study coordinator, and biostatistician, provides scientific and strategic oversight of the trial.

### Composition of the data monitoring committee, its role and reporting structure {21a}

Safety oversight will be under the direction of a Data Safety and Monitoring Board (DSMB) composed of individuals with the appropriate expertise, including physicians in the UI Departments of Neurology and Internal Medicine, and the UI College of Public Health. Members of the DSMB are independent from the study conduct and free of conflict of interest.

### Adverse event (AE) reporting and harms {22}

Possible AEs include: MS relapse, including use of corticosteroids; exacerbation of MS symptoms (pseudo-relapse), no corticosteroids; gastrointestinal (GI) symptoms/side effects; infection (e.g., COVID-19, upper respiratory, urinary tract); non-GI related/other; abnormal lab value(s).

A serious AE is any adverse experience (associated with the study intervention) that results in any of the following outcomes: 1) death; 2) life-threatening adverse drug experience; 3) inpatient hospitalization or prolongation of existing hospitalization; 4) a persistent or significant disability/incapacity; 5) a congenital anomaly/congenital disability; 6) important medical events that may not result in death, be life-threatening or require hospitalization but may be considered a serious adverse drug event when, based upon appropriate medical judgment, may jeopardize the participant and may require medical or surgical intervention to prevent one of the outcomes listed above.

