### Intervention description {11a}

The intervention arms in this study include the MPE diet (Intervention Group 1) and TROO ketogenic diet groups (Intervention Group 2). Participants will be implementing their randomly assigned intervention diet for 24 months. Participants in the two intervention arms will receive education and resources from the study RDNs for their assigned diet and receive continuous support from the study team to facilitate their implementation and adherence to their study diet. Participants assigned to either intervention group will have the opportunity to attend monthly group nutrition counseling sessions led by RDNs. Additional continuous support will include scheduled coaching calls via Zoom after starting the assigned diet to address potential questions. Furthermore, participants in the intervention arms will have access to the UI’s Canvas Classroom, which will serve as a focus group and discussion platform.

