### Usual care control group

Participants assigned to the usual care control group will maintain their current dietary habits and receive educational materials based on the 2020–2025 DGA. To enhance accessibility to these resources, participants will be guided to install the USDA Start Simple with MyPlate mobile application on their phones. Additionally, study participants randomized to the usual care group will receive monthly emails and/or text messages to receive resources with articles, websites, recipes, DGA education materials, and recent MS-related research that does not involve diet.

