### Assignment of interventions: blinding

#### Who will be blinded {17a}

Blinded staff include the PI, all co-investigators, and staff performing study visit assessments. Unblinded staff will include RDNs, study coordinator, and assigned research assistants working with data including, but not limited to, reviewing diet history questionnaires, Life Events (LE), study supplies, and adverse events (AE) reported by study participants. A member of the study team will inform study participants during the informed consent conversation that there will be blinded staff performing study assessments. In addition, statistical analysis of the study data will be performed independently by both a blinded and unblinded statistician.

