### Frequency and plans for auditing trial conduct {23}

The DSMB will meet every six months in joint meetings with the Steering Committee to review cumulative safety and efficacy data from each study arm. The study team will also prepare and submit annual progress reports to the DSMB, summarizing enrollment status, adverse events, protocol deviations, and other relevant metrics. Following each DSMB meeting, the board will provide its recommendations and feedback directly to the PI, who will determine appropriate action in consultation with the Steering Committee. In addition to these formal oversight procedures, the PMG, comprising the PI, study coordinator, senior investigators, RDs, and research staff, meet weekly to monitor ongoing trial operations, address logistical or compliance issues, and ensure that the trial is progressing according to the established timeline and regulatory requirements.

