## Discussion

There is growing evidence that non-pharmacological interventions, particularly dietary interventions, are effective means to manage MS disease progression and symptom severity. Recently, two meta-analyses of randomized dietary intervention trials found a significant impact of dietary interventions on fatigue and QoL among people with MS [8, 79]. One of these meta-analyses [8] resulted in members of the Nutrition Workgroup of the National MS Society recommending a healthy diet as an adjunct therapy for people with MS [80]. Furthermore, a systematic evidence review, conducted by the National Institute for Health and Care Excellence (NICE) to assess the efficacy of non-pharmacological interventions, including diet, in the management of fatigue, found consensus on incorporating diet as a factor in tailored fatigue management recommendations, and underscored the significance of a healthy diet’s impact on overall health in MS [81].

Given the significant knowledge gap in specific dietary recommendations as part of MS care, need for better evidence, and patient demand for evidence-based dietary recommendations, randomized controlled trials with larger sample sizes, longer follow-up, and robust methodology are urgently needed to bridge the knowledge gaps in efficacy as well as the mechanisms by which diet impacts outcomes. Thus, this study protocol describes the design of a randomized, single-blind, controlled design trial, aiming to evaluate the efficacy of incorporating dietary guidance within MS care for improving long-term QoL compared to usual care. Based on the preliminary data obtained from previously conducted trials by our team using the same dietary approaches [22, 23, 82], we expect to see positive short- and long-term benefits on QoL (the primary outcome measure), fatigue, and cognition; however, we have not evaluated MRI in our previous studies and thus have no ability to predict these outcomes. In addition, we expect that these diets will be safe to follow long-term.

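### The serious adverse event definition makes relation to the intervention a condition of seriousness, which can distort serious-event counts by arm

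*Protocol article*

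**What the plan says.** Section {22} of the protocol article first gives examples of adverse events with no causality condition: "Possible AEs include: MS relapse, including use of corticosteroids; exacerbation of MS symptoms (pseudo-relapse), no corticosteroids", followed by gastrointestinal effects, infections, other events and abnormal laboratory values. It then defines the serious subset: "A serious AE is any adverse experience (associated with the study intervention) that results in any of the following outcomes". Six outcomes follow, from death to important medical events.

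Four other places bear on how that definition works:

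- Intervention description {11a}: "The intervention arms in this study include the MPE diet (Intervention Group 1) and TROO ketogenic diet groups (Intervention Group 2").
- Usual care control group, under Dietary education and resources: "Participants assigned to the usual care control group will maintain their current dietary habits and receive educational materials based on the 2020–2025 DGA".
- Who will be blinded {17a}: "Unblinded staff will include RDNs, study coordinator, and assigned research assistants working with data including, but not limited to, reviewing diet history questionnaires". The same list goes on to life events, "study supplies, and adverse events (AE) reported by study participants".
- Frequency and plans for auditing trial conduct {23}: every six months the monitoring board meets to "review cumulative safety and efficacy data from each study arm".

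The Discussion adds "we expect that these diets will be safe to follow long-term".

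**The concern.** Seriousness describes what happened to the participant. Relatedness is a judgement about why. Section {22} requires both before an event is called serious, so a fatal or disabling event that nobody links to the diet drops out of the serious category.

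In a randomised trial the control arm supplies the background rate, so that relatedness need not be guessed case by case. That works only if the same events count in every arm. Here the condition refers to an intervention that, on the wording of {11a}, two arms receive and the third does not. At stake is the serious-event count by arm that the monitoring board sees and that will later be published as evidence on two years of restrictive dieting.

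**Working it through.** **1. The wording.** The parenthesis in {22} qualifies the event before the outcome list is reached. An event is serious if it (a) is linked to the intervention and (b) has one of six outcomes. No other section says that serious events are recorded whatever their cause, and the article does not describe relatedness as a separate attribute.

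**2. Why the arms can differ.** MS relapse and infection are listed as possible adverse events and can occur in any arm. Suppose each leads to an admission. In a diet arm there is a named intervention to which it might be linked. In the control arm there are educational materials and an unchanged diet, so a link is less likely to be drawn. Staff who work with reported events know the allocation ({17a}).

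**3. Arm size.** From Sample size {14}: 36 evaluable per group and 33% attrition. 36 / (1 − 0.33) = 53.73, rounded up to 54; 3 × 54 = 162. Both figures match the article. It states no serious-event rate.

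**4. Illustration on assumed values.** Let p be the true 24-month risk of an event with a serious outcome and a the share judged related, with subscripts D (diet) and C (control).

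Recorded risk difference = p_D × a_D − p_C × a_C

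| Case | p_D | p_C | a_D | a_C | True difference (points) | Recorded difference (points) |
|---|---|---|---|---|---|---|
| Equal risk, low end | 5% | 5% | 30% | 10% | 0 | 1.5 − 0.5 = +1.0 |
| Equal risk, middle | 10% | 10% | 50% | 0% | 0 | 5.0 − 0 = +5.0 |
| Equal risk, high end | 15% | 15% | 50% | 0% | 0 | 7.5 − 0 = +7.5 |
| Diet harmful, equal attribution | 10% | 5% | 30% | 30% | +5.0 | 3.0 − 1.5 = +1.5 |
| Diet harmful, link rarely recognised | 10% | 5% | 10% | 0% | +5.0 | 1.0 − 0 = +1.0 |
| Diet beneficial, unequal attribution | 5% | 10% | 50% | 0% | −5.0 | 2.5 − 0 = +2.5 |

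In the middle equal-risk row the recorded counts are 108 × 0.10 × 0.50 = 5.4 over the two diet arms and 54 × 0.10 × 0 = 0 in control.

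**5. The same row with seriousness set by outcome alone.** Every a becomes 1. The expected counts are 108 × 0.10 = 10.8 over the two diet arms and 54 × 0.10 = 5.4 in control, a difference of 0, as it should be.

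The rows disagree in direction: the definition can raise a false alarm, shrink a real harm or reverse a benefit. Which of these would occur depends on risks and attribution shares that the documents do not give.

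**The case against.** The strongest reply is that the definition governs a label and not data capture. Much of this stands.

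- *Events are not lost.* The list of possible adverse events in {22} has no causality condition. Section {18a} asks participants every three months about medical visits, symptoms, life events and side effects. Section {17b} sends reported medical emergencies to the investigator, the monitoring board and the ethics board. The board's six-monthly review and annual reports in {23} are not limited to serious events. A reader might infer that unrecognised harms are filtered out, or that the board cannot compare the arms. The documents do not support either. But none of these routes corrects the label or is said to give an all-cause serious count by arm.
- *Control counts are not near zero by definition.* The eligibility criteria {10} speak of three study diets, the caption of Table 1 includes the DGA-based usual diet, and controls receive an app and monthly messages. Attribution in the control arm is unlikely but not excluded.
- *Who judges causality is not stated.* Section {17a} says that unblinded staff work with reported events, not that they decide relatedness. Knowledge of the arm can influence the label; that it does is not established.
- *No serious-event test is prespecified.* Safety is not among the outcomes listed in {12}, and {20a} describes no such comparison. The safety sentence in the Discussion is an expectation, not a hypothesis.
- *The article is condensed.* The event forms are not shown and may already hold a relatedness field. That would make correction easier, but the definition as published would still be wrong.

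One could also read the parenthesis loosely, as meaning events that occur during the study. The text does not say so.

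**Conclusion.** The point holds as a defect in a stated definition. Section {22} merges causality with seriousness, and nothing elsewhere in the article undoes it. Because only two arms are named as receiving an intervention and staff who know the allocation work with reported events, the label can be applied unevenly. It can therefore distort serious-event counts in the by-arm safety review under {23} and in later reporting.

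The size is unknown. The range of +1.0 to +7.5 points under equal true risk rests wholly on the assumed risks (5 to 15%) and attribution shares (30 to 50% on diet, 0 to 10% in control). With equal attribution of 30%, a true 5-point harm would appear as 1.5 points. Neither size nor direction can be settled from the documents, so the supportable statement is that the definition can distort the counts, not that it does so in a known direction. The efficacy analyses are not affected.

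**What to change.** 1. In {22}, delete the parenthesis that ties the event to the intervention, so that seriousness depends on outcome alone in all three arms.
2. Keep relatedness as a separate attribute of each event, and state who assesses it and whether that person knows the allocation.
3. Reclassify the adverse events already recorded under the corrected rule. All study activities are expected to end by September 1, 2026 (Trial status), so this can be done before final reporting.
4. For the monitoring board and the final report, tabulate all serious events by randomised arm, with related events as a subset.
5. As a minor drafting point, replace the references to drug events in the outcome list, since no drug is studied.

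The cost is a wording amendment, a possible change to the event form and a one-off review of recorded events. The downside is that more events will be listed as serious.

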### Frequency and plans for auditing trial conduct {23}

The DSMB will meet every six months in joint meetings with the Steering Committee to review cumulative safety and efficacy data from each study arm. The study team will also prepare and submit annual progress reports to the DSMB, summarizing enrollment status, adverse events, protocol deviations, and other relevant metrics. Following each DSMB meeting, the board will provide its recommendations and feedback directly to the PI, who will determine appropriate action in consultation with the Steering Committee. In addition to these formal oversight procedures, the PMG, comprising the PI, study coordinator, senior investigators, RDs, and research staff, meet weekly to monitor ongoing trial operations, address logistical or compliance issues, and ensure that the trial is progressing according to the established timeline and regulatory requirements.

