### Intervention groups

#### Group support sessions

Both the TROO ketogenic and MPE diet groups will receive monthly group nutrition counseling sessions from the intervention RDNs to facilitate long-term diet adherence. Each intervention group will receive monthly live group behavioral support calls, using motivational interviewing, celebrating participant successes, addressing participants’ diet-related questions, to maintain participant engagement in the study. Participants will be invited to submit questions and comments ahead of time so that their concerns can be discussed even if they cannot attend live calls. The study PI will review questions submitted by the study participants in each group and create videos (specific to the intervention group) that address submitted questions. The calls will be recorded and hosted in the Canvas discussion platform. Monthly calls are expected to increase engagement but making them optional and hosting the recorded live coaching calls in the Canvas discussion platform reduces participant burden. Engagement texts and emails tied to holidays and participant birthdays and key study milestones will also be sent. Monthly contacts and engagement contacts are anticipated to enhance participant retention.

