
### Strategies to improve adherence to interventions {11c}

Participants in the MPE diet group will be considered adherent to their diet if DHQ-III survey indicate that they consumed within 20% of recommendations for key intervention diet components (≥ 5 cup equivalent servings of total fruit and vegetables). Adherence to the TROO ketogenic diet will be determined by participants achieving a ketogenic ratio (KR) value of > 1.5 on DHQ-III surveys or by being in nutritional ketosis in 80% of the ketone readings throughout the trial. KR value ≥ 1.5 is considered the minimum threshold to predict a ketogenic diet and will be calculated as follows: (0.9*grams fat + 0.46*grams protein) divided by (0.1*grams fat + 0.58*grams protein + grams total carbohydrate – grams total fiber). In the event the study intervention becomes too restrictive or difficult for the study participant to maintain, the study team has created diet adherence guidelines to give participants options to ease the burden of the study intervention and prevent study discontinuation (Table 2). One of the senior investigators, who has extensive experience conducting long-term, randomized controlled dietary intervention trials, was unblinded and responsible for monitoring and supporting participant adherence to the dietary protocols.

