#### Procedure for unblinding if needed {17b}

In the event of inadvertent unblinding by staff or study participant, the date and circumstance of the unblinding event will be documented. Following the unblinding, the research member of the team that was unblinded will not be allowed to perform any additional assessments on the unblinded study participant for the remainder of the study and a different assessor will be utilized at future study visits. In the case of a medical emergency, the study participant should inform all treating physicians what diet they were assigned for the study. Medical emergencies reported to the study team will be documented by unblinded staff and reported to the PI, Data and Safety Monitoring Board (DSMB), and IRB per Human Subject’s Office (HSO) reporting guidelines. In addition, once the final report has been reviewed by the DSMB, questions have been answered, and requested updates have been made, the DSMB will provide documentation that the PI and additional blinded staff may be provided with the randomized data.

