#### Interim analyses {21b}

Interim analyses will be conducted for DSMB reporting but will not be conducted for presentation or publication.

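### As written, six-monthly joint DSMB and Steering Committee reviews of by-arm efficacy contradict the stated blinding of the PI and co-investigators

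*Protocol article*

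**What the plan says.** Four statements in the protocol article bear directly on the point.

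- Section {23}, on auditing, has the DSMB hold six-monthly "joint meetings with the Steering Committee to review cumulative safety and efficacy data from each study arm". This section also sends the board's recommendations to the PI, who decides what to do in consultation with the Steering Committee.
- Section {5d}, on committees: "The Steering Committee, comprising the PI, senior investigators, study coordinator, and biostatistician, provides scientific and strategic oversight of the trial".
- Section {17a}, on blinding: "Blinded staff include the PI, all co-investigators, and staff performing study visit assessments". It lists the RDNs, the study coordinator and certain research assistants as unblinded, and assigns the analysis to one blinded and one unblinded statistician working independently.
- Section {17b}, on unblinding: once the final report has been reviewed and queries are settled, "the DSMB will provide documentation that the PI and additional blinded staff may be provided with the randomized data".

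Three other places are relevant. Section {21b} says "Interim analyses will be conducted for DSMB reporting but will not be conducted for presentation or publication". Under Group support sessions, the PI reads the questions sent in by each intervention group and records videos for that group. Section {11c} says that one senior investigator "was unblinded and responsible for monitoring and supporting participant adherence to the dietary protocols".

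**The concern.** Sections {17a} and {17b} promise that the PI and co-investigators stay blind until the end of the trial. Section {23} seats the PI and senior investigators at the table while efficacy from each arm is reviewed twice a year. A final report could not state that these people were blinded if the meetings ran as described.

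This matters because of who is exposed. Participants know their diet and report the primary outcome (MSQoL-54) themselves, so what investigators say to them can influence it. The PI records videos for each intervention group and, when re-engagement is needed, sends short video messages to the usual care group. The PI also decides on DSMB recommendations, and the Steering Committee reviews and approves amendments under section {25}. Knowledge of how the arms are doing could affect any of these.

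**Working it through.** The plan gives no figure on this point to reproduce. The check is a comparison of sections, followed by a count of meetings.

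**Who is in the room and what is shown**

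1. Section {23}: DSMB and Steering Committee meet jointly, and the material is accumulating efficacy and safety for each arm.
2. Section {5d}: the committee contains the PI, senior investigators, the coordinator and a biostatistician.
3. From 1 and 2, the PI and senior investigators are present at a by-arm efficacy review.
4. Section {17a}: the PI and all co-investigators are blinded. Section {17b}: they may receive the randomized data only after the final report has been through the DSMB.
5. Steps 3 and 4 conflict. The article mentions no closed session, recusal or coded presentation that would reconcile them.

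For the other members, the coordinator is already listed as unblinded, and the article does not say whether the committee's biostatistician is the blinded or the unblinded one. One senior investigator is stated to be unblinded. The conflict therefore concerns the PI and the remaining senior investigators.

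**Would coded arms remove the conflict?** Coding would be compatible with withholding the randomization table. It would still show blinded investigators whether the arms differ and by how much.

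**How many meetings** (dates from Trial status; assumption: meetings every 6 months from first enrolment)

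- First enrolment 13 April 2022 to planned completion 1 September 2026: 1,602 days / 30.4375 = 52.6 months. 52.6 / 6 = 8.8, so 8 meetings.
- First enrolment to end of recruitment on 22 July 2024: 831 days / 30.4375 = 27.3 months. 27.3 / 6 = 4.6, so 4 of the 8 fall before recruitment closed.
- On this schedule the seventh meeting falls in mid-October 2025, just before publication on 27 October 2025, and the eighth in April 2026.

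**What could be seen, and when**

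- Patient-reported outcomes are collected at baseline and every 6 months (section {18a}). The first meeting, at month 6, would have almost no follow-up quality-of-life data. Later meetings would have progressively more.
- The last participant enrolled reaches month 6 in about January 2025 (July 2024 plus 6 months). Meetings from April 2025 on could show complete 6-month data.
- MRI is done at months 0 and 24 only. The meetings at months 6, 12 and 18 can hold no follow-up MRI, and the one at month 24 almost none.

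**The case against.** The strongest reply is that section {23} gives the meeting format in one sentence of a condensed article. Open and closed sessions, or coded arms, are normally set out in a DSMB charter that is not shown, and access to the randomization table is restricted under section {16b}. Part of this stands: the article describes a plan and does not report that any investigator has seen by-arm results. It does not remove the conflict. The sentence says that the meetings are joint and that arm-level efficacy is reviewed in them, and coding would leave the comparison visible.

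A second reply is that PI blinding protects a self-reported outcome only to a limited extent when participants know their diet, that visit assessors are not listed on the Steering Committee, and that the unblinded coordinator sends the routine control-group texts. This is fair. It narrows the documented routes to the PI's videos and the decisions taken on DSMB recommendations and amendments.

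A reader might infer more than the article supports:

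- *That repeated looks inflate the type I error.* No efficacy stopping rule is stated, and section {21b} ties interim analyses to DSMB reporting. An error rate would require an unadjusted decision rule that the article does not contain.
- *That MRI differences would be on view at every meeting.* The MRI schedule rules this out for the early ones.
- *That the Steering Committee steers the AIC-based model choice.* No section says so, and section {17a} gives the analysis to two statisticians working independently.
- *That the unblinded senior investigator in {11c} contradicts {17a} outright.* It does so only if that person counts as a co-investigator. It may be meant as an exception.

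**Conclusion.** The point holds as an internal contradiction: sections {23} and {5d} cannot be followed together with {17a} and {17b}. If the meetings run as written, the PI and the senior investigators meant to be blinded would see comparative efficacy, chiefly six-monthly self-reported quality of life, at up to about 8 meetings over about 53 months. The investigator blinding would then not hold. The count assumes a regular schedule from first enrolment, and the first meeting or so would show little.

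The size of any resulting bias cannot be derived from the article. Nor does the article show that unblinding has occurred.

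A smaller inconsistency goes with it: a PI listed as blinded handles group-specific questions and videos. That contact need not reveal outcomes by arm, but the blinded list should agree with it.

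**What to change.** 1. Rewrite section {23} and the DSMB charter. The Steering Committee attends an open session limited to pooled enrolment, retention and pooled safety. By-arm safety and efficacy go to a closed session of DSMB members and the existing unblinded statistician. Recommendations reach the PI without by-arm figures.
2. Record who has already seen by-arm efficacy data, when and in what form (named or coded arms), and report this with the results.
3. Bring section {17a} into line with Group support sessions and section {11c}. Either correct the list of blinded staff, or route arm-specific questions and videos through the RDNs, who are already unblinded. State whether the unblinded senior investigator is an exception to the list.

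The cost is protocol and charter wording. No new staff are needed, and the DSMB keeps full by-arm oversight. The downside is that the Steering Committee loses sight of by-arm data. On the assumed schedule, 7 of the 8 meetings fell before publication, so any exposure at those can only be disclosed, not undone.
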